### Suspension criteria

2.6

Subjects may discontinue from the study after discussions with the clinicians for the following reasons:

(1)The subject has an adverse reaction to the intervention.(2)The subject's pain score decreased to 0.(3)The subject wishes to withdraw from the clinical study.(4)The subject wishes to attend other interventions, which may result in the study bias, such as attending chiropractic or other massage therapy or non-traditional spinal treatment.

Those who meet any of the above suspension criteria shall be suspended. However, all subjects’ responses will be recorded to determine the reasons for suspension from the study and the intention-to-treat analysis.

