### Sample size calculation

2.7

This is a randomized controlled trial with 3 parallel arms. The test groups are the TN and T&P groups; the control group is the PT group. The visual analogue scale (VAS) score is the primary outcome. We use ANOVA to calculate the sample size. According to the previous report,^[24]^ the mean (standard deviation) difference of the VAS score of pre- and post-treatment in the TN group, T&P group, and PT group is 1.4 (0.8), 1.9 (0.9), and 1.65 (0.85), respectively. Assuming *α* = 0.05 (2-sided), *β* = 0.80, 171 subjects (57 subjects per group) are needed to achieve an 80% probability of detecting difference (PASS software, Ver. 11, NCSS, LLC. Kaysville, Utah; www.ncss.com). When considering a potential dropout risk of 15%, a total of 204 subjects (68 subjects per group) will be required as a sample size for statistically significant results at each center.

Stratified by 3 centers, the combined sample size is 612 for a meta-analysis.

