### Outcome measurements

2.11

The primary outcome measure assesses the efficacy of massage therapy for the treatment of CNLBP: change in low back pain measured by the 100 mm VAS^[31]^ over the 2-month treatment. Secondary outcome measures included the Oswestry Disability Index^[32]^ (ODI), spinal range of motion^[33]^ (ROM), and the 36-item short-form health survey^[34]^ (SF-36). Fig. 2 demonstrates all measurements and measuring time points.

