### Statistical analyses

2.16

The analysis set will consist of a full analysis set (FAS), a per-protocol set, and a safety set. The safety set will include randomly assigned participants and receive at least one intervention treatment. The FAS will consist of data indicating that the treatment was as close to the intention to treat as possible. In addition to meeting the safety set criteria, the participants must have been evaluated for the primary outcome at least once at the baseline. The FAS will be used in the primary analysis. For missing data, we will analyze the underlying reason and use an imputation adjustment approach, and the last observation carried forward analysis will be used to handle the missing data. After the primary analysis, a sensitivity analysis will be performed by comparing the results from the per-protocol analysis and the intention to treat analysis to evaluate the impact of missing data on the trial results. Besides, subgroup analyses by the center will be done.

(1)Statistical analysis methodFor all of the analyses, SAS version 9.4 was used. The confidence interval will be established at 95%, and the significance level at 0.05.Continuous variables were analyzed with an ANOVA test if normally distributed (results are presented as means ± SD) or Kruskal-Wallis H test if not normally distributed (presented as median with interquartile range). Multiple comparisons were addressed using the Tukey post hoc test (for ANOVA), and Bonferroni correction (for Kruskal–Wallis). The classification count data is checked by the chi-square test. This study used a one-sided test. When *P* < .05, the difference was considered statistically significant.(2)Statistical analysis contenta.Baseline evaluation: Social demographic characteristics, baseline severity analysis.b.Efficacy evaluation: We use the low back pain VAS score sheet, spinal ROM sheet, ODI scale, SF-36 scale, and the number of treatment sessions.c.Safety evaluation: Evaluation was made by the incidence of adverse events or recurrence of pain, or further injury from accidents during the follow-up period, and the level of safety.d.Compliance evaluation: Evaluation was carried out using the compliance rate.

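### The per-protocol versus intention-to-treat comparison is given the job of assessing missing data, which it does poorly: it changes the population too and explores no range of assumptions

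*Protocol article*

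**What the plan says.** The primary outcome is "change in low back pain measured by the 100 mm VAS" over the two-month treatment (section 2.11). Section 2.16 makes the full analysis set (FAS) primary and requires only a baseline value of the outcome for entry. It says reasons for missing data will be examined and an imputation adjustment used, without describing that adjustment, and that "the last observation carried forward analysis will be used to handle the missing data". The sensitivity analysis is then defined as "comparing the results from the per-protocol analysis and the intention to treat analysis to evaluate the impact of missing data on the trial results". A per-protocol set is named but not defined. The analysis by centre in the same section is a subgroup analysis and does not concern missing data.

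Three other sections bear on this:

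- Section 2.7 plans for 15% dropout: "When considering a potential dropout risk of 15%, a total of 204 subjects (68 subjects per group) will be required".
- Section 2.6 lists reasons for leaving that can depend on outcome or arm: an adverse reaction, a pain score of 0, and "The subject wishes to attend other interventions, which may result in the study bias". It adds that the responses of these patients will be recorded.
- Section 2.9 states that patients and therapists are not blinded.

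**The concern.** A sensitivity analysis for missing data should hold the patients and the question fixed and vary what is assumed about the values not seen. The planned comparison moves two things at once. Handling goes from LOCF to exclusion, if the per-protocol set follows the usual convention. The population also changes, because such a set normally removes non-adherent patients whose outcomes were observed. A gap between the two results may therefore reflect adherence, and a small gap may hide a real dependence on the missing outcomes.

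This matters because dropout of 15% is expected, patients know their treatment, and several exit reasons are tied to how the patient is doing. The trial needs to be able to say how robust its pain result is to those exits. The planned check gives little basis for saying so.

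**Working it through.** **Inputs.** Mean changes (SD): "TN group, T&P group, and PT group is 1.4 (0.8), 1.9 (0.9), and 1.65 (0.85), respectively"; two-sided α 0.05; 15% dropout (all section 2.7). VAS units are those of section 2.7, although section 2.11 describes a 100 mm scale. Everything said below about dropouts' outcomes is an assumption.

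**1. The plan's own figure.** Section 2.7 states that "171 subjects (57 subjects per group) are needed to achieve an 80% probability of detecting difference". For a one-way ANOVA with three equal groups, the noncentrality is n × Σ(mean − grand mean)² / SD². The grand mean is 1.65 and the sum of squares is 0.0625 + 0 + 0.0625 = 0.125. With SD 0.85 and n = 57, the noncentrality is 57 × 0.125 / 0.7225 = 9.86 and power is 0.802, so 57 per group reproduces. Then 57 / 0.85 = 67.06, rounded up to 68; 3 × 68 = 204 per centre; 3 × 204 = 612. The sample size is not in question here.

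**2. What the two planned analyses return for T&P minus PT.** Assume the section 2.7 means hold among completers, the per-protocol set is the completers, and only baseline can be carried forward (change = 0).

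| Dropout T&P / PT | LOCF on the FAS | Completers |
|---|---|---|
| 15% / 15% | 0.85 × 1.9 − 0.85 × 1.65 = 1.615 − 1.4025 = 0.2125 | 1.9 − 1.65 = 0.25 |
| 20% / 10% | 0.80 × 1.9 − 0.90 × 1.65 = 1.52 − 1.485 = 0.035 | 0.25 |

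Unequal dropout opens a visible gap. With equal dropout LOCF only multiplies the difference by 0.85, so the results lie close together by construction.

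**3. What the full data could be at 15% / 15%.**

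- Dropouts like completers in both arms: 0.25.
- No change in dropouts of either arm: 0.2125.
- T&P dropouts unchanged, PT dropouts like PT completers: 0.85 × 1.9 + 0.15 × 0 − 1.65 = −0.035.

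The planned pair covers the first two assumptions. It does not cover the third, where the sign changes.

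**4. The same arithmetic with nothing missing.** Suppose every outcome is observed, and the 15% of T&P patients who do not change are non-adherent instead of lost. Intention-to-treat then gives −0.035 and per-protocol 0.25. That gap is wide with no missing value at all. In step 3 the two planned results differed by only 0.0375 while the missing values could move the answer below zero. The size of the gap therefore does not measure the impact of missing data.

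**5. What a tipping-point analysis would report.** Lower the missing T&P outcomes by δ, with the other arm's dropouts like its completers. Significance is lost at δ = (c × SE − difference) / 0.15, where SE = 0.85 × √(2/n) and c is the Tukey critical value on the scale of a t statistic.

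- 204 per arm: SE 0.0842, c 2.349, c × SE = 0.198. T&P minus PT: (0.198 − 0.25) / 0.15, about −0.35. T&P minus TN: (0.198 − 0.50) / 0.15, about −2.0.
- 68 per arm: SE 0.1458, c 2.361, c × SE = 0.344. T&P minus TN: (0.344 − 0.50) / 0.15, about −1.0. T&P minus PT is not significant even without a shift (0.25 / 0.1458 = 1.71).
- If the SE uses the observed patients only (0.85 × 204 = 173.4 per arm), it is 0.0913, and the T&P minus PT shift becomes (2.349 × 0.0913 − 0.25) / 0.15, about −0.24.

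These are approximations using a common SD of 0.85. The planned comparison gives no figure of this kind. Section 2.16 also says "This study used a one-sided test", which conflicts with section 2.7 but has no bearing on this point.

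**The case against.** The strongest objection is that the comparison does vary something. Carrying baseline forward assumes dropouts did not change; excluding them treats completers as representative. These are two different assumptions, and the results respond: 0.035 against 0.25 when dropout is 20% and 10%. This stands. The check is not empty, and it can flag dropout that differs between arms.

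A reader might go further and infer that the check is worthless because it returns the same pair of results whatever the dropouts' true outcomes were. That does not follow. No analysis of observed data depends on unobserved values, and multiple imputation and a tipping-point table would not either. Their advantage is that they show results over a range of stated assumptions.

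A reader might also quote a much larger swing. If dropouts in one arm improved by 4 and those in the other by 0, the full-data difference would be 1.615 + 0.60 − 1.4025 = +0.8125, or 1.615 − 1.4025 − 0.60 = −0.3875 the other way round. But 4 lies (4 − 1.9) / 0.9 = 2.3 SD above the T&P mean, and the documents give no ground for it.

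The baseline-only premise is also open to doubt. Section 2.14 lists assessments at baseline, end of treatment and three months later. Yet section 2.6 names a pain score of 0 as an exit reason, section 2.12 has symptoms reviewed before and after each session, and the Figure 2 schedule is not shown. If pain is scored during treatment, LOCF would carry those values and 0.2125 and 0.035 would change. The mixing of population and handling would remain.

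Finally, this is a condensed article. A SAP may define the per-protocol set and add analyses, so nothing here shows that the trial has no other missing-data analysis, nor that its report will claim robustness. What remains is the purpose that the article itself assigns to this comparison.

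**Conclusion.** The point holds in a limited form. Section 2.16 gives the per-protocol versus intention-to-treat comparison a purpose it serves poorly. It makes a single switch in handling, changes the population along with it, and does not show how far the assumption about missing outcomes must move before the conclusion changes.

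On the plan's figures at an equal 15% dropout, two results as close as 0.2125 and 0.25 are compatible with a full-data T&P minus PT difference of about −0.035. This rests on baseline being the only value to carry, on a per-protocol set made up of completers, and on T&P dropouts not changing while PT dropouts resemble PT completers. It illustrates what the check can miss and does not predict what will happen.

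The documents do not support saying that the check can detect nothing, or that both analyses make the same assumption about the missing values.

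**What to change.** Replace the sentence in section 2.16. Make the missing-data sensitivity analysis multiple imputation under missing-at-random on the FAS, followed by a delta-adjusted (tipping-point) version that shifts the imputed end-of-treatment VAS separately by arm. Report the shift at which the conclusion changes. Keep the per-protocol analysis as a supplementary analysis of adherence, and define that set. If a SAP already contains such analyses, the article's stated purpose should be aligned with it.

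The cost is one paragraph and a little more programming with standard procedures in SAS, which the plan already uses. It needs no new data and no more patients.

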### Randomization

2.8

In this study, we will use a blocked randomization method. Each site will run the randomization independently, and the same randomization method will be adopted. A statistician will use SAS 9.4 (SAS Institute Inc., Cary, NC) with a “proc plan” program to produce the randomizing scheme. After production, the scheme will be signed and sealed by the staff who produces it and kept by other staff participating in this trial. It will not be allowed to be checked by anyone except the Principal Investigator. Physicians in each center will be responsible for getting random numbers.

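### The primary VAS analysis uses a change-score ANOVA with a distribution-dependent switch and no baseline covariate, which gives up precision the trial already has and leaves the handling of centre unresolved

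*Protocol article*

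**What the plan says.** The primary outcome in section 2.11 is "change in low back pain measured by the 100 mm VAS" over the 2-month treatment, so the analysed variable is a change score.

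Section 2.16 gives one rule for all continuous variables: "Continuous variables were analyzed with an ANOVA test if normally distributed", shown as means with SD, or a "Kruskal-Wallis H test if not normally distributed", shown as medians with interquartile range. Multiple comparisons use Tukey after ANOVA and Bonferroni after Kruskal-Wallis. No covariate and no centre factor is named.

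Baseline VAS is available for every patient analysed: to enter the FAS, "the participants must have been evaluated for the primary outcome at least once at the baseline". Its only other mention in the analysis section is under baseline evaluation, as "Social demographic characteristics, baseline severity analysis".

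On centre, three statements stand apart:
- Section 2.8: "Each site will run the randomization independently, and the same randomization method will be adopted".
- Section 2.7: "Stratified by 3 centers, the combined sample size is 612 for a meta-analysis".
- Section 2.16: "subgroup analyses by the center will be done", with no other use of centre.

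**The concern.** Three features of the stated method cost something.

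1. **Baseline.** Subtracting baseline fixes its coefficient at 1. ANCOVA estimates the coefficient, and with equal variances at the two times it is more precise whenever the correlation is below 1. The inclusion criteria set no minimum pain score, so baseline values may spread widely.
2. **The switch.** Which test is used depends on how the data look. A switch changes the reported effect from means to medians and the multiplicity method from Tukey to Bonferroni, and this is settled only after the data are seen. The sample size in section 2.7 was built on group means, and a rank test does not estimate a difference in means.
3. **Centre.** Patients are randomised within site. If the primary result is one pooled ANOVA without centre, the standard errors include between-centre variation that the design has already balanced out. If it is the meta-analysis mentioned in section 2.7, they do not. The protocol does not say which applies.

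At stake are the precision of the pairwise comparisons, notably TN against PT, and a single effect measure fixed in advance.

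**Working it through.** **Inputs.** From section 2.7: mean (SD) VAS change 1.4 (0.8) for TN, 1.9 (0.9) for T&P and 1.65 (0.85) for PT; alpha 0.05 two-sided; 80% power; 57 per group per centre; 15% dropout; 68 per group per centre; 3 centres. Assumed, because the document does not give them: the baseline to follow-up correlation r, equal variances at the two times, and the share of variance lying between centres.

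**1. The plan's own figure.** For the one-way ANOVA F test with common SD 0.85, the noncentrality is n × Σ(μᵢ − μ̄)² / SD² = 57 × (0.25² + 0.25² + 0) / 0.7225 = 9.86. With 2 and 168 degrees of freedom, power is 80.2%. Then 57 / 0.85 = 67.1, rounded up to 68 per group, 204 per centre and 612 in all. The stated sample size reproduces. Pooled over three centres at 3 × 57 = 171 per arm, the same omnibus test has 99.9% power.

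**2. Variance with baseline as a covariate.** Let s² be the VAS variance at each time.
- Change score: 2s²(1 − r).
- ANCOVA: s²(1 − r²).
- Ratio: (1 + r) / 2, which is 0.65, 0.75 and 0.85 for r = 0.3, 0.5 and 0.7.
- Effective SD: 0.85 × √ratio = 0.685, 0.736 and 0.784.

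**3. Power for one pairwise contrast.** Either test arm differs from PT by 0.25 (1.65 − 1.4, or 1.9 − 1.65). The noncentrality is 0.25 / (SD × √(2/n)). The Tukey critical value for three groups on the t scale is about 2.35. Two values of n are shown: 171 per arm (completers) and 3 × 68 = 204 per arm (everyone randomised, the most the FAS with last observation carried forward could hold).

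| Analysis | n = 171: noncentrality | Tukey power | n = 204: noncentrality | Tukey power |
|---|---|---|---|---|
| Change-score ANOVA | 2.72 | 64% | 2.97 | 73% |
| ANCOVA, r = 0.3 | 3.37 | 85% | 3.68 | 91% |
| ANCOVA, r = 0.5 | 3.14 | 78% | 3.43 | 86% |
| ANCOVA, r = 0.7 | 2.95 | 73% | 3.22 | 81% |

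Without the Tukey adjustment, power at 171 per arm goes from 77% to 92%, 88% and 84%. At 204 per arm the change-score ANOVA has 84%. The n = 204 columns assume that carrying values forward leaves the mean difference and SD unchanged.

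**4. Centre.** If a fraction c of the variance lies between centres and centre is left out of a pooled ANOVA, the reported standard error is too large by about 1/√(1 − c). For c = 0.02, 0.05 and 0.10 this is 1.010, 1.026 and 1.054, or about 1% to 5%. In simulated trials with centre left out, type I error at nominal 5% was 4.3%, 3.9% and 2.2% for c = 0.05, 0.10 and 0.20. The error is on the conservative side.

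**The case against.** **Baseline is not ignored.** A reader might infer that the plan throws baseline VAS away or leaves chance imbalance uncorrected. It does neither outright: a change score subtracts baseline, and under randomisation change-score ANOVA is as valid as ANCOVA. This stands. The point is only the gap in precision between the two.

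**The trial was not sized on a pairwise contrast.** Section 2.7 sizes an omnibus three-group test within each centre. That figure is right, and the pooled omnibus test has ample power. A reader might take the 64% as proof of an under-powered trial. The document does not support that, because the 0.25 contrast was not the sizing target. It is still the contrast the trial will be read for, since the discussion describes a comparison of TN with PT.

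**Centre may already be handled.** If ANOVA is run within each centre and the results are combined by the meta-analysis of section 2.7, centre is conditioned on and the standard-error point falls away. Nor does the word ANOVA exclude a centre factor. Both arguments stand, so what remains is that sections 2.7 and 2.16 do not agree.

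**Model terms may sit in the analysis plan.** A condensed article may leave covariates to a document that is not shown. That tempers the point about unnamed terms. It does not reach the switch, which is written out with its own summary measures and corrections. However, no formal normality test is named, so it cannot be claimed that a switch will certainly be triggered.

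**Conclusion.** The concern holds as a matter of efficiency and prespecification. As written, the primary analysis is a change-score ANOVA with no stated baseline covariate and a fallback chosen by the data. Adjusting for baseline would cut the variance by 35%, 25% or 15% at r = 0.3, 0.5 or 0.7. For a 0.25 pairwise contrast under Tukey, that is worth roughly 8 to 20 percentage points of power at 171 per arm and 8 to 18 at 204.

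These gains rest on an assumed r, equal variances, SD 0.85 and pooling over centres. The cost of leaving out centre is small, about 1% to 5% on the standard error if 2% to 10% of the variance lies between centres (assumed), and arises only if the primary result is a single pooled ANOVA.

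A reader might go further and conclude that the sample size is wrong or that type I error is inflated. Neither follows: the sample size reproduces for the test it names, and leaving centre out makes the test conservative.

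**What to change.** In section 2.16:
- Prespecify one primary model that does not depend on a normality check: an ANCOVA of 2-month VAS (or its change) on arm, baseline VAS and centre. Report adjusted mean differences with 95% confidence intervals.
- Keep Kruskal-Wallis as a sensitivity analysis only.
- Use the same model form for continuous secondary outcomes that have a baseline value.
- Reconcile with section 2.7 by stating whether the centres are pooled in this model or combined in a stratified meta-analysis of baseline-adjusted centre estimates.

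The cost is wording. Baseline VAS and centre are already recorded, and neither the sample size nor the data collection has to change.

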**Methods::**

This is a multicenter, assessor-, and analyst-blinded, randomized controlled trial with 3 parallel arms: TN, PT, and TN combined with PT (Tuina combined with physiotherapy) group. Six hundred twelve eligible CNLBP patients will be randomly assigned to the groups in a 1:1:1 ratio in 3 centers. The TN intervention includes 9-step routine techniques, while the PT intervention includes a physiotherapy treatment plan based on a patient's symptoms. The interventions for both groups will last for 30 minutes and will be carried out for 6 sessions in 8 weeks. The primary outcome will be the visual analog scale pain score. And the secondary outcomes will include the Oswestry Disability Index, spinal range of motion, 36-item short-form health survey. Safety evaluation will be recorded during the whole study. All data in this randomized controlled trial will be analyzed by SAS 9.4.

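### Section 2.16 declares one-sided testing at P<.05, which contradicts the two-sided 5% alpha of section 2.7 and the 95% interval beside it, and gives no direction

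*Protocol article*

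**What the plan says.** Protocol article, section 2.7 (Sample size calculation): alpha is 0.05 and explicitly two-sided. The method is given as "We use ANOVA to calculate the sample size". The planning means (SD) of VAS change for TN, T&P and PT are "1.4 (0.8), 1.9 (0.9), and 1.65 (0.85), respectively", and 57 evaluable subjects per group "are needed to achieve an 80% probability of detecting difference".

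Protocol article, section 2.16 (Statistical analyses): "The confidence interval will be established at 95%, and the significance level at 0.05". The section then names ANOVA or Kruskal-Wallis for continuous outcomes, Tukey (after ANOVA) or Bonferroni (after Kruskal-Wallis) for multiple comparisons, and chi-square for categorical data. It closes with "This study used a one-sided test" and says that when P is below .05 "the difference was considered statistically significant". It states no direction, no directional hypothesis and no one-sided level of 0.025.

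**The concern.** Sidedness is part of the significance criterion for the primary outcome, and the article gives two versions of it. The one-sided version also clashes with the confidence level in its own paragraph and does not fit the tests listed there.

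An analyst who wanted to follow section 2.16 literally would have to decide what 'one-sided' means for a three-group comparison, for which pairs, and in which direction. If those choices are made after the data are seen, the error rate is no longer the stated 5%. If they are made in the mildest way, readers will still see a one-sided claim beside 95% intervals and a two-sided sample size, and will not know which threshold was used.

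**Working it through.** **Step 1. Reproduce the sample size, to see which criterion the design used.** Inputs from section 2.7: means 1.4, 1.9 and 1.65, taken with a common SD of 0.85 (my assumption: the middle of the three SDs); alpha 0.05; power 80%. Equal allocation is from the abstract.
- Grand mean = (1.4 + 1.9 + 1.65)/3 = 1.65. Deviations are −0.25, +0.25 and 0, and their squares sum to 0.125.
- Effect size f = √(0.125/3)/0.85 = 0.204/0.85 = 0.240.
- With n = 57 per group, the noncentrality is 57 × 0.125/0.85² = 9.86 on 2 and 168 degrees of freedom. Power of the 5% F-test is 80.2%.
- Dropout: 57/(1 − 0.15) = 67.1, rounded up to 68. Then 68 × 3 = 204 per center and 204 × 3 = 612.

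This matches the stated "171 subjects (57 subjects per group" and everything that follows from it. An F-test at 10%, which is what halving its P value amounts to, would need only 46 per group; one at 2.5% would need 68 evaluable per group. Of these three levels, only the ordinary 5% F-test gives 57.

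**Step 2. Test against interval.** A two-sided 95% interval for a single contrast excludes zero when |z| > 1.960. A one-sided 5% test rejects when z > 1.645, which corresponds to a 90% two-sided interval. Any contrast with z between 1.645 and 1.960 is therefore significant by the test while its 95% interval includes zero. A one-sided P of 0.04 is an example: the two-sided P is 2 × 0.04 = 0.08.

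**Step 3. Does 'one-sided' fit the tests named?**
- Three-group ANOVA F, Kruskal-Wallis H and chi-square with more than one degree of freedom reject for departures in any direction. They have no direction to choose.
- The standard Tukey procedure covers two-sided differences for all pairs.
- The word can therefore have a numerical effect only through halved P values or one-sided pairwise tests, and section 2.16 describes neither.
- The planning means give TN − PT = 1.4 − 1.65 = −0.25 and T&P − PT = 1.9 − 1.65 = +0.25. No single direction relative to PT fits both test arms.

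**Step 4. Size of the effect if P values were halved under the planned Tukey adjustment.** Halved P < 0.05 means unhalved P < 0.10. With three groups and 168 degrees of freedom, the critical value for a pairwise t statistic falls from 2.365 to 2.066. Error rates with no true differences (simulation, 57 per group, 400,000 runs):

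| False claim | Tukey, two-sided 5% | Tukey, P halved |
|---|---|---|
| One named direction (TN better than PT) | 0.96% | 2.0% |
| Either test arm better than PT | 1.8% | 3.7% |
| Any pair, direction chosen after the data | 5.0% | 10.0% |

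On the Kruskal-Wallis route, three-pair Bonferroni gives the same pattern. For either test arm falsely better than PT, the bound moves from 2 × 0.05/6 = 1.67% to 2 × 0.05/3 = 3.33%.

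**Step 5. The benign reading.** If 'one-sided' only records that F and chi-square reject in the upper tail, every rate in the table stays in its first column.

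**The case against.** The strongest reply is that nothing is inflated. The omnibus tests keep their 5% level unless someone halves a P value, the plan never says to halve one, and the sentence may be a loose description of upper-tail rejection. The 0.05 level and the 95% interval are already stated, and the sample size reproduces. This stands in part: the doubling is conditional, and I give it only as conditional. It does not rescue the sentence, which as written still contradicts section 2.7.

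A reader might also infer stronger things that the document does not support:
- *Unadjusted error rates.* Without adjustment, one directional claim goes from 2.5% to 5%, and a false benefit claim for either of two test arms from 4.5% to 8.8%. Section 2.16 fixes Tukey and Bonferroni, so these figures describe an analysis that is not planned. Under halved Tukey P values with the direction fixed in advance as benefit, a false claim against PT stays below 5%.
- *Twice the error rate the trial was sized on.* The trial was sized on an omnibus F-test, which has no rate per direction to double.
- *The test could not show TN to be worse than PT.* This presumes that the tested direction is TN better. No direction is stated, so it is a possibility only.
- *The plan assumes TN is worse.* The means are planning values taken from an earlier report, not a hypothesis. They show only that one direction does not suit both arms.

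**Conclusion.** The contradiction is real, and nothing elsewhere in the article resolves it. As stated, the significance criterion for the primary outcome is ambiguous, and the one-sided wording is incompatible with the 95% interval and ill-suited to the tests named.

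Its effect on error rates ranges from none (upper-tail reading) to about a factor of two (halved or one-sided pairwise P values). In absolute terms under Tukey, the worst case is 10% instead of 5%, and it requires the direction to be chosen after seeing the data. These rates assume normal outcomes with equal variances, 57 evaluable per group as at one center, and no true differences. Step 1 indicates that the design was built on the ordinary 5% criterion, so section 2.16 is the passage to bring into line.

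**What to change.** In section 2.16, replace the one-sided sentence with: *All tests are two-sided at the 5% level, with 95% confidence intervals.* This matches section 2.7 and the interval already specified, and leaves the Tukey and Bonferroni procedures as they are. Make the change before the data are analyzed and record it as a protocol amendment.

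The cost is one sentence. No patients are added: 57 evaluable and 68 randomized per group per center, and 612 overall, were already obtained at the 5% level. The only thing given up is the more lenient threshold that a one-sided pairwise test would have allowed.
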